**SUMMARY:**

|                         |                                                                                                                                                                                                                                                                                                                                                                                                                                                                                                                                                                                                                                                             |
|-------------------------|-------------------------------------------------------------------------------------------------------------------------------------------------------------------------------------------------------------------------------------------------------------------------------------------------------------------------------------------------------------------------------------------------------------------------------------------------------------------------------------------------------------------------------------------------------------------------------------------------------------------------------------------------------------|
| Title                   | “Retrospective observational study of the administration of Jusvinza according to the action protocol of CUBA for the management of COVID-19 at the [name] Soto Hospital”                                                                                                                                                                                                                                                                                                                                                                                                                                                                             |
| Patient population      | Patients $\geq 19$ years of age, who were positive to SARS-CoV-2 by RT-PCR, classified as moderate, severe and critically ill patients, according to the action protocol of Cuba for the management of COVID-19                                                                                                                                                                                                                                                                                                                                                                                                                                             |
| Rationale of the study  | Patients with COVID-19 that progress toward the more severe stages of the disease show a marked hyper-inflammation that can lead to cardiovascular collapse and multiple organ failure and produce death. In this setting, we recommend the identification and treatment of hyper-inflammation with the aim of reducing mortality. In Cuba we use the drug Jusvinza for the treatment of moderate, severe and critical COVID-19 patients. Jusvinza is an immunomodulator peptide with anti-inflammatory properties.                                                                                                                                         |
| Objectives of the study | General objective: To observe its effectiveness in the reduction of hyper-inflammation and the safety of the administration of Jusvinza in patients having COVID-19 whose condition was classified as moderate, severe and critical.
Specific objectives 

• Describe the clinical progress of the high-risk patients towards severe or critical stages or death

• Describe the progress of the inflammatory markers of the patients included in the study.

• Describe the radiologic progress of the patients included in the study.

• Describe the adverse events.

 |
| Hypothesis              | On considering that with the extensive study of the use of Jusvinza in Cuba, 85 % of the severe patients recovered, we expect that 90% of the high-risk patients treated with Jusvinza will not progress to the severe conditions of the disease and will recover.                                                                                                                                                                                                                                                                                                                                                                                          |
| Main variables          | Percentage of high-risk, severe and critical patients recovering after the treatment with Jusvinza.                                                                                                                                                                                                                                                                                                                                                                                                                                                                                                                                                         |
| Secondary variables     | 

1. Describe the clinical evolution of the patients.

2. Describe the radiological evolution.

3. Quantify the inflammatory biomarkers in the serum (NLR, C-reactive protein, erythrocyte sedimentation, Ferritin, LDH, D-dimer, CPK, ASAT, ALAT).

4. Quantify the cytokines: IL-6, TNF<math>\alpha</math> and IL-10.

5. Quantify the percentage of lymphocytes CD4, CD8 and Treg.

6. Presence and characterization of adverse events.

                                                                                                                                 |

Approved by:

[name] [name]

Signature:

[figure not shown]

Cargo:

Director of Biomedical Research, CIGB

Date:

13/05/2021

|                                       |                                                                                                                                                                                                                                                                                                                |
|---------------------------------------|----------------------------------------------------------------------------------------------------------------------------------------------------------------------------------------------------------------------------------------------------------------------------------------------------------------|
| Design of the study                   | Retrospective, observational, monocentric study
We will collect the retrospective information of each patients using the clinical records as the source of primary information, as well as clinical laboratory results and radiologic imaging stored in the GALEN program of the participating institution. |
| Number of patients                    | We will include all positive patients to SARS-CoV-2 by RT-PCR with the available information, classified as of high-risk, severe and critical conditions, who were prescribed the use of Jusvinza.                                                                                                             |
| Frequency and duration of the therapy | According to the indications of the Action Protocol                                                                                                                                                                                                                                                            |
| Drug under study                      | Drug: Jusvinza (2.5 mg or 1.25 mg), intravenous administration.                                                                                                                                                                                                                                                |
| Safety evaluation                     | 

• Symptoms

• Vital signs

• Analytical results

• Imaging results

                                                                                                                                                                        |

---

Approved by:

[name] [name]

Signature:

[figure not shown]

Cargo:

Director of Biomedical Research, CIGB

Date:

13/05/2021

## LIST OF ABBREVIATIONS USED AND DEFINITION OF THE TERMS

GCP: Good Clinical Practices: A standard for the design, conduction, implementation, monitoring, auditing, recording, analysis and reporting of clinical trials that offer the assurance that the data and the results reported are credible and accurate, and that the rights, integrity and confidentiality of the subjects of the study are protected. (Extracted from regulation 21 – 08: requirements for the authorization and modification of clinical trials. CECMED)

CECMED: Center for the State Control of Drugs, Medical Equipment and Devices.

ESRC / ERC: Ethics for Scientific Research Committee / Ethics and Review Committee.

CIGB: Center for Genetic Engineering and Biotechnology.

DRF: Data Recording Form.

Adverse event: It is defined as any unfavorable medical incident occurring to a subject participating in a clinical trial after the administration of a pharmaceutical product. This incident may not necessarily have a causal relationship with the treatment. An adverse event may therefore be an unfavorable or unexpected sign (e.g. an abnormal laboratory finding), symptom or disease that is temporarily associated with the use of a medicinal product. (Extracted from the Guidelines on Good Clinical Practices, CECMED, 2000)

Unexpected adverse event: Any adverse event in which the specificity or severity is not consistent with the risk information described in the protocol or in the researcher's handbook (if there is one). It also refers to an adverse event that has not been previously observed.

Jusvinza: immuno-modulating peptide CIGB-258.

MINSAP: Ministry of Public Health.

RT-PCR: Real Time Polymerase Chain Reaction.

Adverse reaction: It refers to an adverse event that is considered to be related in a causal manner with the research product; this includes overdose and interactions with other drugs. Any undesired harmful response produced by a pharmaceutical product at any dose, should be considered an adverse reaction to drugs. One well accepted definition of a reaction to drugs is found in the Technical Report of the World Health Organization (Series No. 850, 1995) that states: "and adverse reaction is a harmful and

Approved by:

[name] [name]

Signature:

[figure not shown]

Cargo:

Director of Biomedical Research, CIGB

Date:

13/05/2021

unintended response to a pharmaceutical product that occurs at a dose that is normally used in persons for prophylaxis, diagnosis, therapy, or to modify a physiological function. In clinical trials, the damage caused by overdose, abuse or dependence, and interactions with other products, should be considered adverse reactions”.

SARS-CoV: Severe Acute Respiratory Syndrome-Coronavirus.

---

**1.9. Ethics and Review Committee**

The biomedical study will be carried out retrospectively, taking into account the available data from the clinical records of the patients treated with Jusvinza.

The source of information for data collection are the Clinical Records and the clinical laboratory results and the available imaging results of each patient through the GALEM program. The approval from the Ethics Committee will be obtained for accessing the information of the patients.

The protocol will be presented in the public registry of clinical trials of CENCEC.

---

Approved by:

[name] [name]

Signature:

[figure not shown]

Cargo:

Director of Biomedical Research, CIGB

Date:

13/05/2021

## II. INTRODUCTION

### 2.1. Main data on the problem and its context.

Patients having COVID-19 that progress towards severe and critical conditions present a marked hyper-inflammation. This stage of the disease is mediated by a high concentration of pro-inflammatory cytokines, a biological event known as the “cytokine storm”. As the hyper-inflammation progresses, these patients can reach cardiovascular collapse and multiple organ failure that would lead to death (i,ii)

In this setting, the identification and treatment of hyper-inflammation is recommended, with the aim of reducing mortality. In Cuba, we use the drug named Jusvinza for the treatment of moderate, severe and critical COVID-19 patients. Jusvinza is an immuno-modulator peptide with anti-inflammatory properties. The peptide was developed at the CIGB for the treatment of autoimmune diseases, specifically for rheumatoid arthritis (RA) (iii).

This peptide was shown to increase the frequency of regulatory T cells (Treg) with the phenotype CD4+CD25highFoxp3+ in *ex vivo* assays with peripheral blood mononuclear cells (PBMC) from patients with RA (rheumatoid arthritis), but not in healthy donors; these cells have a suppressing activity (iv). Furthermore, on administering the drug through the subcutaneous route, the peptide induces a significant increase of the Treg cell population showing phenotype CD4+Foxp3+ in the lymphatic nodes, in contact with the administration site, and in the spleen of BALB/c mice. Moreover, this peptide efficiently inhibits inflammation in arthritis models (v).

On the other hand, the pharmacokinetic and biodistribution studies through three routes, intravenous, intradermal and subcutaneous routes, demonstrated that the peptide has a broad distribution towards different organs, which include the gastrointestinal tract, liver, lungs, etc. The maximum concentration in the blood is reached after half an hour and its clearance occurs at approximately 6 hours (vi). Toxicology studies in three animal species demonstrate that the peptide has a good safety profile.

These results at the preclinical research stage resulted in the authorization granted by the Regulatory Authority for Drugs, Medical Equipment and Devices of the Republic of Cuba (CECMED) for the evaluation of the peptide in a phase I clinical trial in patients with RA (RPCEC00000238). In this phase I clinical trial, the product showed its safety, pharmacokinetic profile and there was preliminary evidence of its therapeutic effect (vii,viii, ix). At present, we are processing the results of a Phase II

---

Approved by:

[name] [name]

Signature:

[figure not shown]

Cargo:

Director of Biomedical Research, CIGB

Date:

13/05/2021

clinical trial in patients with RA (RPCEC00000230), to evaluate the efficacy and safety of this therapeutic candidate. This is a controlled, randomized and triple blind trial with 187 patients. We have observed a good safety profile.

This set of results endorsed the granting for the compassionate use of Jusvinza by CECMED in the treatment of critical patients with COVID-19 (RPCEC00000313). The action protocol with Jusvinza was started on March 31, 2020, in the intensive care unit (ICU) of the Luís Díaz Soto Military Hospital, of Havana. The medical specialists described in their reports that as of 48 hours of the treatment with Jusvinza, the patients started showing clinical, gasometrical and radiologic improvement. These 12 patients were extubated and they recovered; they continue under a strict surveillance in their health areas. The laboratory parameters indicated that the patients had lymphopenia and a trend towards neutrophilia before starting the treatment. However, during the course of the treatment, the levels of lymphocytes and neutrophils reached their normal values. At the same time, the markers associated to hyper-inflammation (C-reactive protein, ferritin, dehydrogenase lactate, fibrinogens, creatinine and transaminases) were normalized during the treatment. The concentration of the three cytokines involved in the cytokine storm (IL-6, TNF- $\alpha$ , IL-1 and IL-10) were normalized during the course of the treatment (x). These results and the safety profile of Jusvinza enabled led to the authorization for its use in the treatment of severe COVID-19 patients, and the inclusion of Jusvinza will be approved for the national treatment protocol in severe and critically ill patients.

The introduction of Jusvinza in the national protocol approved by the Ministry of Public Health for the treatment of severe and critical cases of COVID-19, took place on April 27, 2020, as well as the extension of its use in all Cuban hospitals with COVID-19 cases. The use of Jusvinza has had an impact in decreasing the lethality rate in Cuba. The lethality rate in April of 2020 in Cuba was of 4.16 (xi) and in March of 2021 it was of 0.46 (xii).

The treatment with Jusvinza has been safe for the patients. Molecular studies made in Cuba, when extending the use of Jusvinza to all hospitals with COVID-19 patients, have confirmed the results obtained during the compassionate use study. It was demonstrated that the treatment with Jusvinza is able to reduce hyper-inflammation in COVID-19 patients. The administration of Jusvinza in severe patients prevents the progression of these cases to a critical phase of the disease. The effectiveness of the treatment in severe patients surpasses 86%. The levels of C-Reactive Protein (CRP) decrease

Approved by:

[name] [name]

Signature:

[figure not shown]

Cargo:

Director of Biomedical Research, CIGB

Date:

13/05/2021

significantly in patients at 72 hours after the treatment. A significant inverse correlation was found between the improvement of the ventilating parameters and the CRP in critical patients with invasive mechanical ventilation. Other inflammation biomarkers such as ferritin, dehydrogenase lactate, creatinine and transaminases, decrease significantly. Several studies report that these patients are characterized because of their neutrophilia and lymphopenia, with a neutrophil/lymphocyte ratio (NLR) above 5.1 (xiii). The treatment with Jusvinza reduced NLR to normal values. Furthermore, it reduced the levels of Calprotectin, a protein secreted by monocytes and neutrophils during inflammatory processes (xiv). The reduction of the Calprotectin was significantly correlated to the decrease of neutrophils. Moreover, reports show that the deregulation of the immune response in COVID-19 patients is associated to an increase in Granzyme B and Perforin, and a decrease in the percentage of Treg (xv, xvi). The results of our patients indicate a significant decrease of Granzyme B and Perforin, at 96 hours of the treatment, coinciding with the decrease of interleukins IL-6, IL-10 and TNF- $\alpha$ . The percentage of Treg increased at 48 hours of the treatment in the severe patients studied (xvii). The increase of the Treg in COVID-19 patients is consistent with the mechanism of action of Jusvinza in patients with RA (iii,iv).

The overall results made it possible to conclude that the treatment with Jusvinza decreases the hyperinflammation that characterizes the patients with COVID-19.

### III. OBJECTIVES

#### 3.1. General Objective

- To observe its effectiveness in the reduction of hyper-inflammation and the safety of the administration of Jusvinza in patients having COVID-19 whose condition was classified as moderate, severe and critical.

#### 3.2. Specific objectives

1. Describe the clinical progress of the high-risk patients towards severe or critical stages or death
2. Describe the progress of the inflammatory markers of the patients included in the study.
3. Describe the radiologic progress of the patients in the study.

---

Approved by:

[name] [name]

Signature:

[figure not shown]

Cargo:

Director of Biomedical Research, CIGB

Date:

13/05/2021

4. Describe the adverse events.

### 3.3 Hypothesis

On considering that with the extensive study of the use of Jusvinza in Cuba, 85 % of the severe patients recovered, we expect that 90% of the high-risk patients treated with Jusvinza will not progress to the severe conditions of the disease and will recover.

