## VIII. EVALUATION VARIABLES

### 8.1. Protocol variables

#### 8.1.1. Main variables

#### ❖ Evaluation of the anti-inflammatory effect:

Approved by:

[name] [name]

Signature:

[figure not shown]

Cargo:

Director of Biomedical Research, CIGB

Date:

13/05/2021

- ✓ We will calculate the percentage of high-risk patients recovering after a seven-day treatment with Jusvinza.
- ✓ We will calculate the percentage of severely ill patients recovering after a ten-day treatment with Jusvinza.
- ✓ We will calculate the percentage of critically ill patients recovering after a fifteen-day treatment with Jusvinza.

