## 8.2. Criteria for the success or failure of the individual, and of the therapy

- ☐ We will consider an **individual success** if the patient recovers; if there are no severe adverse events with a demonstrated causality.
- ☐ We will consider a **therapeutic success** if the hypothesis is demonstrated, in which 90% of the high-risk patients treated with Jusvinza do not reach the severe phases of the disease and then recover.
- ☐ We will consider an **individual failure** when a patient progresses toward a more severe condition or death and if there is a definitive interruption of the treatment due to the presence of severe adverse events, with a causal relationship attributable to the product under study.
- ☐ We will consider a **therapeutic failure** when patients progress towards the more severe stages of the disease.

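### The 90% hypothesis requires non-progression and recovery, but the main variable for high-risk patients counts recovery alone, so a main result of 90% or more cannot confirm it

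*Protocol*

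**What the plan says.** **Hypothesis.** Protocol 3.3, repeated in the Summary: "we expect that 90% of the high-risk patients treated with Jusvinza will not progress to the severe conditions of the disease and will recover". No day is attached. The only basis given is that "85 % of the severe patients recovered" in earlier use of the drug.

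**Success rule.** Section 8.2 counts the therapy as successful "if the hypothesis is demonstrated", restated there as "90% of the high-risk patients treated with Jusvinza do not reach the severe phases of the disease and then recover".

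**Main variable.** Section 8.1.1: "We will calculate the percentage of high-risk patients recovering after a seven-day treatment with Jusvinza". Parallel lines follow for severe patients (ten days) and critical patients (fifteen days). The Summary gives "Percentage of high-risk, severe and critical patients recovering after the treatment with Jusvinza", without a day.

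**Where progression appears.** Specific objective 1 in 3.2 is to "Describe the clinical progress of the high-risk patients towards severe or critical stages or death", and the first secondary variable in 8.1.2 is the patients' clinical evolution. Progression is in neither statement of the main variable.

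**Individual success.** Section 8.2 grants it "if the patient recovers; if there are no severe adverse events with a demonstrated causality". Non-progression is not required.

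**The concern.** The hypothesis and the success rule concern one proportion, and the designated main variable is another. The two differ for any high-risk patient who becomes severe or critical and then recovers. Preventing that progression is what the hypothesis is about, so the main variable is blind to the event of most interest.

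Recovery of 90% or more could be read as meeting the hypothesis when the two-part proportion is below 90%. This matters because 8.2 declares success or failure of the therapy, and 14.1.1 has the results sent to the regulator for the product's registration file.

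The basis of the 90% adds to the problem. It is argued from recovery in severe patients, which is another severity class and another endpoint. Less ill patients can be expected to do better whatever the drug does, so reaching 90% in them would not by itself point to a drug effect.

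**Working it through.** **1. Definitions side by side (high-risk patients).**

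| Place | Must not progress | Must recover | Time |
|---|---|---|---|
| 3.3 and Summary, hypothesis | yes | yes | none |
| 8.2, therapeutic success | yes | yes | none |
| 8.1.1, main variable | no | yes | seven days, meaning unclear |
| Summary, main variable | no | yes | none |
| 8.2, individual success | no | yes, and no causally related severe adverse event | none |

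**2. Is there a figure to reproduce?** No. The protocol gives no step from 85% (severe, recovery) to 90% (high-risk, two-part outcome), and 11.1 takes all eligible patients with information, without a number. Every R, q, S and n below is therefore an assumption.

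**3. Relation between the quantities.** Let R be the proportion recovering, q the share of recovered patients who had progressed first, and C the two-part proportion. Over the same window, with patients kept in their starting class:

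C = R × (1 − q), so C ≤ R.

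| R | q = 0 | q = 2% | q = 5% | q = 10% | largest q with C ≥ 90%, 1 − 0.90/R |
|---|---|---|---|---|---|
| 0.90 | 0.900 | 0.882 | 0.855 | 0.810 | 0% |
| 0.92 | 0.920 | 0.902 | 0.874 | 0.828 | 2.2% |
| 0.95 | 0.950 | 0.931 | 0.902 | 0.855 | 5.3% |
| 0.98 | 0.980 | 0.960 | 0.931 | 0.882 | 8.2% |

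For example, 0.92 × 0.95 = 0.874.

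**4. Would separate reporting settle it?** Not fully. If R and the non-progression proportion S are given only as separate percentages, then max(0, R + S − 1) ≤ C ≤ min(R, S). With R = S = 0.90, C lies anywhere from 0.80 to 0.90. The two outcomes have to be combined within patient.

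**5. Effect on the conclusion.** Take an observed proportion of at least 90% as the mark, with X binomial(n, p). Use p = 0.92 for recovery and p = 0.874 for the composite.

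| n (assumed) | needed | main variable | composite |
|---|---|---|---|
| 50 | 45 | 0.792 | 0.385 |
| 100 | 90 | 0.824 | 0.271 |
| 200 | 180 | 0.878 | 0.158 |
| 400 | 360 | 0.938 | 0.065 |

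The gap widens with n, because the two measures estimate different proportions.

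**6. The two readings of the seven days.** If they are the length of the course, recovery is an upper bound on the composite: a result below 90% counts against the hypothesis, while 90% or more leaves it open. If they are an assessment day, a patient who never progresses and recovers later fails the main variable yet satisfies the hypothesis, so a result below 90% would not refute it either. On both readings, 90% or more does not confirm it.

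**7. If class is not fixed at the start.** The protocol does not say that it is. If patients who progress are moved to the severe group, the high-risk percentage R′ is taken among those who did not progress. Then C = R′ × S, which is again no larger than the reported figure.

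**The case against.** The strongest reply is that the protocol does contain the right quantity. Section 8.2 states the composite as the success rule, 3.2 has progression to severe or critical stages or death described, and 8.1.2 covers clinical evolution. Section 8.2 also mentions progression under individual failure, though its wording leaves open whether interruption for adverse events is needed as well. This reply stands against any claim that the hypothesis is untestable, which a reader might infer. It does not make the designated main variable the quantity on which success is declared.

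A reader might also infer that the main variable is recovery by day 7, so that a patient well on day 9 is always misclassified. The text does not settle that: the parallel ten-day and fifteen-day lines, and the Summary's wording without a day, fit course length at least as well. The day-9 case applies only under the other reading.

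A third tempting step is to fault the plan for not excluding 85%. The protocol sets no such test in high-risk patients, and the 85% belongs to another class and endpoint. Whether the word demonstrated in 8.2 refers to a point estimate or a confidence limit can be left to a statistical analysis plan, so its absence here is no fault.

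Finally, the stated aims in 3.1 and 3.2 are to observe and describe. That is so, but 8.2 still draws a verdict on the therapy, and that verdict needs one defined quantity.

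**Conclusion.** The concern holds in this form: the main variable for high-risk patients is not the outcome in the hypothesis and the success rule, and a main result of 90% or more cannot confirm the hypothesis. Under the assumed 92% recovery with 5% of recovered patients having progressed first, the composite is 87.4%, which is 4.6 points lower. An observed 90% or more then has probability 0.82 against 0.27 at an assumed n of 100. The size depends on how often patients progress and then recover, which the protocol does not give; at q = 0 there is no gap. The mismatch in definitions does not depend on these values.

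The basis of the 90% is a separate, lesser matter. It leaves the target without support for this class and endpoint, but it is not what prevents the main variable from confirming the hypothesis.

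**What to change.** - **Main variable.** For patients classed as high-risk at first dose, use the proportion who did not reach the severe or critical class, did not die, and recovered, all over one stated window. Use the same words in the Summary, 3.3, 8.1.1 and 8.2. Keep recovery alone as a reported component.
- **Seven days.** State whether this is a course length or an assessment day.
- **Reporting.** Give the composite with an exact 95% confidence interval. At an assumed 90 of 100 it would run from 82.4% to 95.1%.
- **Status of the 90%.** Call it a descriptive target. Say that its only stated basis is recovery in severe patients and that reaching it is not evidence of a drug effect. Do not use 85% as the success bar, since that figure comes from the wrong class and endpoint.

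**Cost.** Mostly wording and one interval. The headline percentage can only stay the same or fall relative to recovery over the same window, so 90% becomes harder to reach. The recording form must also be checked: the table in 10.1 lists test results, imaging, product administration and adverse events, but does not name change of severity class. If the form does not capture it, it has to be added and taken from the clinical records.
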